### P_4_mNC-FBT group

On days 8–12 of the menstrual cycle (MC), depending on the length of the patient’s MC, transvaginal ultrasound is used to monitor follicular development and endometrial growth. Vaginal micronized progesterone (Utrogestan, Besins, Belgium) is started at 200 mg in the afternoon and 200 mg in the evening when the dominant follicle reached ≥16 mm and the endometrial thickness is at least 7 mm. A blastocyst is transferred on day 5 after the addition of progesterone. On day 14 after blastocyst transfer, serum *β*-hCG levels are measured. Upon positive serum pregnancy testing, progesterone support will continue until 8–10 weeks of gestation. However, afternoon progesterone use is eliminated for 30 days after embryo transfer.

### HRT-FBT group

Endometrial preparation will begin on the second day of the menstrual cycle with oral estradiol (E_2_) valerate at a dose of 2 mg twice daily. When the patient’s endometrial thickness is ≥7 mm, vaginal progesterone administration will be initiated at a dose of 200 mg 3 times daily. On day 5 of the progesterone administration, blastocysts are thawed and transferred. For patients with endometrial thickness <7 mm, patients continued oral E_2_ until the endometrium is ≥7 mm. On day 14 after blastocyst transfer, serum *β*-hCG levels are measured. Upon positive serum pregnancy testing, E_2_ and progesterone supplementation is continued for 8–10 weeks of gestation.

### Randomization and blinding

Statistical professionals not involved in the study will complete the randomization groupings using software (R 4.0.0, R Foundation for Statistical Computing, Vienna, Austria), and stratify by female age (<35 or ≥35 years). Patients will then be randomized in a 1:1 ratio to the P_4_mNC-FBT and HRT-FBT groups. Both the investigators and patients will be aware of the allocation. Blinding of the intervention is impossible for patient and doctors administering it. To minimize performance and reporting biases arising from the absence of blinding, embryologists and doctors involved in embryo transfer are blinded to the group assignments of the participants. Subjective outcomes, such as pregnancy complications, were assessed by strictly adhering to internationally recognized diagnostic guidelines to ensure objectivity. Additionally, patients received standardized instructions for symptom reporting to avoid discrepancies in self-described experiences.

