### Eligibility criteria

#### Inclusion criteria

Patients aged 21 to 44 years undergoing FBT;Body mass index (BMI) 18–35 kg/m^2^;Having regular ovulatory cycles.

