## Statistics

### Non-inferiority design and power calculation

A non-inferiority design is used as the new treatment, P_4_mNC-FBT, is expected to yield comparable results, but will offer significant advantages over the current standard treatment (HRT-FBT) in terms of patient convenience, reduced incidence of gestational hypertensive disorders, and lower costs as the progesterone dosage is reduced. In a previous study, the LBR is 45% in the P_4_mNC-FBT group and 39.6% in the HRT-FBT group (18). Sample sizes of 302 in P_4_mNC group and 302 in HRT group achieve 80.069% power to detect a difference of 0.05 when the non-inferiority difference is −0.05. The reference group proportion is 0.4. The treatment group proportion is assumed to be 0.35 under the null hypothesis. The power was computed for the case when the actual treatment group proportion is 0.45. The test statistic used is the one-sided Z test (unpooled). The significance level of the test is 0.05. A total of 672 patients are finally included in both groups, taking into account a 10% dropout rate.

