### Statistical analysis

ITT analyses include drop-outs and canceled cycles, PP analyses include canceled cycles but not drop-outs, and per-transfer analyses exclude both drop-outs and canceled cycles. Differences in LBR will be evaluated by means of risk differences with one-sided 95% CI (or equivalently two-sided 90% CI). Non-inferiority will be concluded if the CI excludes a difference of more than 5% in favor of the present standard treatment (HRT-FBT) in ITT and PP analyses. Depending on the characteristics of the baseline data, continuous data will be expressed as mean ± SD or median and interquartile spacing (IQR). Categorical data will be described by frequencies and percentages. The primary outcome, LBR, will be compared between the two groups using the *χ*^2^ test as well as risk ratios and 95% CI. Quantitative variables will be analyzed using the student *t*-test or Mann–Whitney test. Secondary outcomes will be compared between the two arms using the similar approach described for the primary outcome. Data will be analyzed using SPSS 26.0 and a *p*-value <0.05 will be considered statistically significant. Any missing data will be handled using pairwise deletion.

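### Randomisation is stratified by female age, but the primary live-birth analysis is written without the stratum: a minor, conservative loss of precision that a wording change removes

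*Protocol article*

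**What the plan says.** Under Randomization and blinding, the protocol article states that the allocation will "stratify by female age (<35 or ≥35 years", and then: "Patients will then be randomized in a 1:1 ratio to the P_4_mNC-FBT and HRT-FBT groups". It does not say how balance is kept within each age stratum, for example by blocks. The Inclusion criteria admit a wide age range ("Patients aged 21 to 44 years undergoing FBT"), so both strata can be filled.

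Under Statistical analysis, the decision quantity is given as: "Differences in LBR will be evaluated by means of risk differences with one-sided 95% CI (or equivalently two-sided 90% CI". Non-inferiority needs that interval to exclude a deficit of more than 5 points in both the ITT and the PP analysis. The same section adds a test: "The primary outcome, LBR, will be compared between the two groups using the" chi-square test, with risk ratios. None of these is described as stratified or age-adjusted.

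The sample size section also ignores strata: "The test statistic used is the one-sided Z test (unpooled"; "The significance level of the test is 0.05". The article gives no LBR by age, no expected age split and no stated reason for choosing age as the factor.

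**The concern.** Stratified randomisation with balance inside each stratum takes the between-stratum variation in outcome out of the treatment comparison. The usual two-proportion variance formula still counts that variation. If the factor is prognostic, the crude standard error is therefore larger than the true one, the lower confidence bound sits too low, and the test runs below its nominal error rate.

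Here that bound decides the trial. Planned power is only just above 80%, and it assumes a true 5-point advantage for the new regimen, so precision has some value. The PP set adds a further reason: it removes drop-outs, and the age balance created at randomisation need not survive that exclusion. A stratified estimate accounts for a resulting imbalance between the two age groups; a crude one does not.

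**Working it through.** **Inputs from the article (Non-inferiority design and power calculation).** Control LBR 0.40; treatment LBR 0.45 under the alternative and 0.35 under the null; margin 0.05; one-sided alpha 0.05 (z = 1.645); 302 per arm; 10% dropout.

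**The plan's own figure.** Unpooled variance sum: 0.40×0.60 + 0.45×0.55 = 0.4875. SE = √(0.4875/302) = 0.0402. Power = Φ(0.10/0.0402 − 1.645) = 80.07%, which reproduces the stated 80.069%. Then 302/0.9 = 335.6, rounded up to 336 per arm, or 672 in total. The stated sample size therefore follows from the unstratified formula.

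**Assumptions, not in the documents.** Half the women are under 35. LBR differs between the age strata by d, equally in both arms. The overall rates stay at 0.40 and 0.45. For d = 0.20, for example, control LBR is 50% and 30% in the two strata. Allocation is balanced within strata.

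**Formulas.** With a 50:50 split, each arm's within-stratum variance is the total less d²/4, so the two-arm sum falls by d²/2.

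- Stratified SE: SE_s = √((0.4875 − d²/2)/302)
- Power of the crude test in the same age-balanced trial: Φ((0.10 − 1.645×0.0402)/SE_s)
- Power of the stratified test: Φ(0.10/SE_s − 1.645)
- One-sided error of the crude test at the null (variance sum 0.24 + 0.2275 = 0.4675): 1 − Φ(1.645×√(0.4675/(0.4675 − d²/2)))

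| Age gap d | Variance sum within strata | SE ratio | 90% CI half-width, crude → stratified (points) | Power, crude | Power, stratified | Gain (points) | Error of crude test |
|---|---|---|---|---|---|---|---|
| 0 | 0.4875 | 1.000 | 6.61 → 6.61 | 80.1% | 80.1% | 0 | 5.0% |
| 10 points | 0.4825 | 0.995 | 6.61 → 6.57 | 80.2% | 80.4% | 0.2 | 4.9% |
| 20 points | 0.4675 | 0.979 | 6.61 → 6.47 | 80.6% | 81.5% | 0.9 | 4.6% |
| 30 points | 0.4425 | 0.953 | 6.61 → 6.30 | 81.2% | 83.3% | 2.1 | 4.2% |

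**Sensitivity.** With 70% of women under 35 and a 20-point gap, power is 80.5% crude and 81.3% stratified, and the crude error is 4.7%. At 336 per arm, a 50:50 split and a 20-point gap, power is 84.2% and 85.0%.

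**Simulation check** (200,000 replicates per setting, 50:50 split). The direction is the same and the gains are a little smaller: 81.1% against 81.4% at a 20-point gap, and 81.5% against 82.2% at 25 points. The crude error was 4.6% and 4.4%.

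**The case against.** The strongest reply is that an unadjusted two-proportion comparison is valid, matches the method used to size the trial, and errs on the safe side for a non-inferiority claim. All of that stands. The planned power was computed without strata, so it is reached without adjustment, and the point estimate is not biased by design.

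It can also be said that a condensed article may leave adjustment to an analysis plan that is not shown. That stands in part. The article does not merely stay silent, however: it names a plain chi-square test and a risk difference, so a plan that used the stratum would have to depart from the published wording.

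A reader might infer stronger conclusions, which the documents do not support:

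- **That power rises from 80.1% to 81.5% or 83.3%.** This measures the gain from the planning figure. In a trial balanced on age, the crude test itself has 80.6% or 81.2% power at gaps of 20 or 30 points. The 80.1% is the crude power only if stratification does not enforce balance, and then the error stays at 5%. The larger gain and the lower error rate cannot both hold.
- **That the interval is certainly too wide and the error certainly below 5%.** Both need enforced balance within strata, which the article does not state. With simple allocation inside strata, the crude interval has nominal coverage and is only less efficient.
- **That the loss equals about 10% more patients.** This belongs to the 30-point gap alone (0.4875/0.4425 = 1.10). At 20 points the figure is about 4% (0.4875/0.4675 = 1.04).
- **That age was chosen because it predicts live birth.** This is plausible but not stated.

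**Conclusion.** The point holds as a minor matter of efficiency and of consistency between design and analysis. The stratification factor is not carried into the primary estimate, interval or test. For assumed age gaps of 10 to 30 points at a 50:50 split, the cost is about 0.2 to 2.1 points of power and an interval about 0.5% to 5% wider than needed. It is zero if LBR does not differ by age. The one-sided error of about 4.9% to 4.2% is conservative and depends on balanced allocation within strata. No false claim of non-inferiority becomes more likely, and the sample size is adequate as calculated. The documents cannot settle which row of the table applies, because they give neither age-specific rates nor the age split.

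**What to change.** In the Statistical analysis section:

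- Define the primary estimate as the risk difference in LBR stratified by the randomisation stratum (<35 / ≥35), either by Mantel-Haenszel or standardised from a logistic model containing the stratum. Compare its one-sided 95% lower bound with −5% in both ITT and PP.
- Replace the plain chi-square test with a stratified (Cochran-Mantel-Haenszel) test.
- Keep the unstratified difference as a sensitivity analysis.
- If age imbalance inside a stratum is also to be corrected, for example among women of 35 to 44, put continuous age in the model. Mantel-Haenszel on two strata does not do this.
- State how allocation is balanced within strata.

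The cost is a change of wording made before outcomes are compared. Age is already needed for randomisation, so no new data are required, and the sample size does not change. The article names SPSS 26.0 for analysis and R only for randomisation, so the software sentence may need a small addition if the chosen estimator is run elsewhere.

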### Data collection and management

Relevant treatment data for patients will be collected at the appropriate time points: (1) baseline (MC 2–4 days); (2) day of blastocyst transfer (same day); and (3) *β*-hCG (14 days after blastocyst transfer). Follow-up data for all pregnancies resulting from FET will begin with inclusion in the study and continue for 1 year, according to the study protocol. Based on the anonymous subject ID numbers used in the trial, the database has a complete audit trail. Participant information sheets will be prepared to ensure data accuracy and regular data monitoring and validation, and data will be backed up once a day (on another computer in the same physical location as the server).

## Statistics

### Non-inferiority design and power calculation

A non-inferiority design is used as the new treatment, P_4_mNC-FBT, is expected to yield comparable results, but will offer significant advantages over the current standard treatment (HRT-FBT) in terms of patient convenience, reduced incidence of gestational hypertensive disorders, and lower costs as the progesterone dosage is reduced. In a previous study, the LBR is 45% in the P_4_mNC-FBT group and 39.6% in the HRT-FBT group (18). Sample sizes of 302 in P_4_mNC group and 302 in HRT group achieve 80.069% power to detect a difference of 0.05 when the non-inferiority difference is −0.05. The reference group proportion is 0.4. The treatment group proportion is assumed to be 0.35 under the null hypothesis. The power was computed for the case when the actual treatment group proportion is 0.45. The test statistic used is the one-sided Z test (unpooled). The significance level of the test is 0.05. A total of 672 patients are finally included in both groups, taking into account a 10% dropout rate.

### Statistical analysis

ITT analyses include drop-outs and canceled cycles, PP analyses include canceled cycles but not drop-outs, and per-transfer analyses exclude both drop-outs and canceled cycles. Differences in LBR will be evaluated by means of risk differences with one-sided 95% CI (or equivalently two-sided 90% CI). Non-inferiority will be concluded if the CI excludes a difference of more than 5% in favor of the present standard treatment (HRT-FBT) in ITT and PP analyses. Depending on the characteristics of the baseline data, continuous data will be expressed as mean ± SD or median and interquartile spacing (IQR). Categorical data will be described by frequencies and percentages. The primary outcome, LBR, will be compared between the two groups using the *χ*^2^ test as well as risk ratios and 95% CI. Quantitative variables will be analyzed using the student *t*-test or Mann–Whitney test. Secondary outcomes will be compared between the two arms using the similar approach described for the primary outcome. Data will be analyzed using SPSS 26.0 and a *p*-value <0.05 will be considered statistically significant. Any missing data will be handled using pairwise deletion.

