## Objectives

### Primary objective

The primary objective of the study is to investigate if P_4_mNC-FBT is non-inferior to standard HRT-FBT in terms of LBR. ITT and per-protocol (PP) analyses will be performed with a non-inferiority margin of 5%. A live birth is defined as the delivery of any surviving newborn at 28 weeks or more of gestation.

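### The stated per-protocol set removes only drop-outs, so its half of the non-inferiority rule gives little protection against dilution from regimen switching or protocol deviations

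*Protocol article*

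**What the plan says.** The Statistical analysis section defines three sets by two attributes, drop-out and canceled cycle:

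- ITT: "ITT analyses include drop-outs and canceled cycles".
- PP: "PP analyses include canceled cycles but not drop-outs".
- Per-transfer: "per-transfer analyses exclude both drop-outs and canceled cycles".

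The decision rule follows: "Non-inferiority will be concluded if the CI excludes a difference of more than 5% in favor of the present standard treatment". The same sentence requires this in both ITT and PP, and the Primary objective section also names both sets with the 5% margin. The per-transfer set is not part of the rule.

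The article does not define drop-out. It does not say how PP treats a woman who receives the other preparation, proves ineligible or has a major deviation.

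**The concern.** In a non-inferiority trial, women who receive the other regimen pull the arms together, which favors the claim. A per-protocol analysis is required beside ITT so that the claim does not rest only on a contrast weakened in this way. A set selected on drop-out status alone is a completers set. A woman allocated to P4mNC but prepared with HRT, or the reverse, who stays in follow-up meets no stated PP exclusion. She counts under her allocated arm in both required analyses.

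Two features of the design make this worth settling. The Randomization and blinding section says that patients and investigators know the allocation. The P4mNC-FBT group section starts progesterone "when the dominant follicle reached ≥16 mm and the endometrial thickness is at least 7 mm" and does not say how a woman who fails to reach this point is classed for analysis.

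**Working it through.** **Inputs from the Non-inferiority design and power calculation section.** HRT live birth rate 0.40; P4mNC rate 0.35 under the null and 0.45 under the alternative; margin 0.05; one-sided unpooled Z test at level 0.05 (z = 1.645); 302 per arm; 10% dropout; 672 in total. The share s of P4mNC women who receive HRT is **not given**, so a range is assumed.

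**1. The plan's own figures.** Power = Φ[(pT − pC + 0.05)/SE − 1.645], with SE = √[pC(1 − pC)/n + pT(1 − pT)/n].

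- SE = √[(0.24 + 0.2475)/302] = 0.0402.
- Power = Φ(0.10/0.0402 − 1.645) = 0.8007, which matches the stated 80.069%.
- 302/0.90 = 335.6, so 336 per arm and 672 in total.

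The design figures reproduce. None of them depends on the PP definition.

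**2. Switchers kept in the P4mNC arm.** Take the difference as received to be exactly at the margin (0.35 vs 0.40) and give switchers the HRT rate. The arm rate becomes pT = 0.35 + 0.05s, the observed difference becomes −0.05(1 − s), and

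P(claim) = Φ(0.05s/SE − 1.645).

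For s = 10%, SE = √[(0.24 + 0.355 × 0.645)/302] = 0.0394, and Φ(0.005/0.0394 − 1.645) = 0.0645.

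| Assumed s | Difference (points) | PP, 302 per arm | ITT, 336 per arm |
|---|---|---|---|
| 0 | −5.00 | 5.0% | 5.0% |
| 5% | −4.75 | 5.7% | 5.7% |
| 10% | −4.50 | 6.5% | 6.5% |
| 20% | −4.00 | 8.2% | 8.4% |
| 30% | −3.50 | 10.3% | 10.7% |

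Simulation at 302 per arm gave 5.0%, 6.5% and 8.2% for s = 0, 10% and 20%. If the same share switches in both directions (HRT arm rate 0.40 − 0.05s), the PP figures are 6.5%, 8.2% and 12.8% at 5%, 10% and 20%.

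The ITT column assumes that all 336 women per arm are analyzed at the same rates. The chance of passing both analyses cannot exceed the smaller of the two figures; how far below it lies depends on the overlap of the sets and was not computed.

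**3. What the stated PP set does remove.** If 10% drop out of each arm and ITT counts them as no live birth, the rates become 0.35 × 0.90 = 0.315 and 0.40 × 0.90 = 0.36. The difference shrinks to −4.5 points and the chance of a claim in ITT (336 per arm) is 6.6%. Removing drop-outs avoids this.

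**4. Switchers excluded.** If exclusion is unrelated to prognosis, the rate at the margin returns to 5.0%. If it is related, it need not. As an assumed illustration, let 10% of women have a live birth rate of 30% under HRT and the rest 41.1% (0.9 × 41.1 + 0.1 × 30 = 40.0), with P4mNC lowering the rate by 5 points when used. If that 10% switch to HRT:

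- Kept: 0.9 × 36.1 + 0.1 × 30 = 35.5% against 40%, a difference of −4.5 points and a claim in about 6.5%.
- Excluded from the P4mNC arm only: 36.1% against 40%, a difference of −3.9 points and a claim in about 8.5%.

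**The case against.** **Retention of switchers is inferred.** The article never says that switchers, ineligible women or protocol violators stay in PP. Drop-out is undefined and might cover some of them, and a fuller document may list deviations. This stands as a limit on the wording. It does not remove the point, because the article does state a PP definition and makes that set half of the confirmatory rule.

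**The joint rule is not worthless.** A reader might infer that it gives no protection against dilution at all. Step 3 shows otherwise: PP removes the dilution from drop-outs. A reader might also infer from the pairwise deletion of missing data that ITT and PP are practically the same set. The article says that ITT includes drop-outs and does not settle how the two statements combine, so the point does not rest on that.

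**Switching may be rare.** The treatment sections describe no conversion between regimens, and the inclusion criteria require regular ovulatory cycles. A P4mNC cycle that never meets its criteria may simply be canceled, which the definitions already cover. A reader might infer that cross-over is to be expected; the documents give neither a route nor a rate. This stands, and it is why every figure above is conditional on an assumed share.

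**The excess is against one contrast only.** At s = 20% the as-randomized difference is −4.0 points, inside the margin, so an ITT claim is not false for that question. This is correct. The inflation is against the contrast between regimens as received, which a per-protocol analysis is meant to address.

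**Excluding switchers can bias too.** Step 4 shows that exclusion linked to prognosis in one arm can favor non-inferiority. This stands and shapes the fix.

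**Conclusion.** The point holds in a limited form. The stated PP set excludes only drop-outs and has no adherence, eligibility or deviation criterion, so as written it gives little protection against dilution from regimen switching or protocol deviations. It does protect against dilution from drop-outs.

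The size is modest at low switching and grows with it: from 5% to about 5.7%, 6.5% or 8.2% in PP for an assumed 5%, 10% or 20% one-way switching. These figures rest on a true as-received difference exactly at the margin, switchers having the HRT rate, and 302 per arm. The sample size calculation is unaffected. This is a definition worth correcting before outcomes are compared; it is not evidence that switching will occur.

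**What to change.** - Define drop-out.
- Define PP as randomized women who met eligibility and were managed with their allocated preparation, including cycles canceled under it. Exclude cross-overs and major deviations by written criteria fixed before outcomes are compared.
- Keep the present set, renamed completers, as a sensitivity analysis.
- Leave ITT and the joint ITT and PP requirement unchanged.
- Record the preparation actually received, and report the number of switchers and the reasons by arm.

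The cost is a change of analysis wording and one recorded item. PP becomes smaller, but the sample size need not change for this point alone if the exclusions fit within the 10% allowance. PP is also selected after randomization, and exclusions linked to prognosis in one arm could bias it in either direction, so it should not be relied on alone.
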